**Intervention group**																
	Explain the study, ask for consent, administer the questionnaire (Multimedia Appendix 1)	✓														
	Register the cell phone number of the parent in the CIMA^c^ database	✓														
	SMS education message			✓		✓	✓		✓							
	SMS reminder for the appointment										✓					
	Automatically scheduled reminder 1 week prior the appointment												✓			
	Mark in the CIMA registry if the newborn came back on time												✓			
	SMS reminder for parents that have missed the appointment														✓	
**Control group**																
	Explain the study, ask for consent, administer the questionnaire (Multimedia Appendix 1)	✓														
	Register the expected date for the second contact (for comparison with the intervention group)	✓														
	Mark the date when the newborn came back to the clinic												✓			

^a^First contact.

^b^Second contact.

^c^CIMA: Children Immunization App.

### Control Group

Participants in the control group will continue to receive regular routine messages from the health facility. After obtaining consent, we will use the same procedure to give ID numbers to the babies in the control group, except that the letter *C* (for “control”) will be used instead of *I*. The control group will receive usual care at the clinic. For example, the vaccination nurse will review the schedule of vaccine appointments at the end of the month, then call parents that have missed their baby’s appointment to remind them about the second contact vaccine appointment and to invite them to come back to the clinic. No educational messages and no SMS reminders will be sent out to the participants enrolled in the control group.

### Measures

The key measures for this study are the percentage improvement in parent-child units who return for follow-up visits and the percentage improvement in children who receive immunization as scheduled. We will send reminders to the parents of children that do not come back to their appointments within 1 week after the scheduled appointment.

### Data Collection

At the time of study enrollment, we will approach parents of newborns coming for their first immunization dose. In the intervention and control arms, we will collect baseline information using a questionnaire (Multimedia Appendix 1). As we plan to monitor adherence to vaccination appointments from birth to the age of 6 months, we will use the clinic ID number to monitor visits using the clinic health care records for both study groups.

Both clinical visits and vaccination attendance will be collected from the health facility registration records. Informed consent will be obtained at the baseline visit from clients after an explanation of the study purpose and the data analysis. No personal identifiers will be collected (ie, names or personal addresses), but we will collect the phone numbers of one of the parents, as this will be used to send the SMS messages. All data will be stored in a secured location. No financial compensation will be offered to the parents, and they will have the choice to ask to stop being enrolled in the study.

### Data Collection Tool

Data will be collected from the clinic registration books for the upcoming second contact appointment visit. The baseline questionnaire (Multimedia Appendix 1) will be used to collect basic demographic and household information, including the type of household (rented house, rented apartment, informal settlement, other, or no answer), date of birth of the father and mother, level of education of the father and mother (don’t know how to read and write; know how to read and write; primary or elementary school; secondary school; postschool technical level; university level; don’t know or don’t remember, or refused to answer), the availability of a private toilet inside the household (yes or no); professional status of the father and mother (full-time job, part-time or hourly job, self-employed, do not work, returned, or refused to answer), total number of children living at home, who is the decision-maker for vaccination (both parents, mother, father, or other); total number of children younger than 5 years at home; and amount of money spent by the household in the month prior the date of the interview.

### Data Analysis

The data analysis will be conducted in 3 steps. First, we will summarize the characteristics of the babies and their parents using a general descriptive statistical analysis and compare these characteristics between the intervention and control groups. We will use the Fisher exact test to detect any statistically significant differences in the key measures between the intervention and control groups (*P* values <.05 will be considered statistically significant). Second, we will calculate the attrition rate of the babies and compare the attrition rate in each of the intervention and control groups. Third, we will compare how often both study groups return for 1 follow-up visit using a Kaplan-Meier survival analysis. We will determine the proportion of babies that did come back on time at the end of each week to help the clinic to visually identify the proportion of latecomers and which geographical areas they live in. We will use R (R Core Team) for the statistical analysis. For the descriptive analysis, we will use the *dplyr* library package in R; for the Fisher exact test, we will use the *stats* library package; for the Kaplan-Meier survival analysis, we will use the *survival* library package.

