**Methods:**

This will be a nonrandomized controlled trial that will be conducted at Azire Integrated Health Centre, Bamenda, Cameroon.

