### Intervention and Control Groups

The recruitment will be done through two steps. In step 1, the intervention group will be recruited. Then, in step 2, when the sample size is achieved, recruitment of the control group will be conducted until we reach the required sample size.

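### The key measures are tested with a crude Fisher exact test in a nonrandomised comparison, so confounding by baseline covariates that are collected in both arms is left in the result

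*Protocol article*

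**What the plan says.** The design is stated in the Abstract (Methods): "This will be a nonrandomized controlled trial that will be conducted at Azire Integrated Health Centre, Bamenda, Cameroon". Under Intervention and Control Groups, the intervention group is recruited to full size first. The article continues: "Then, in step 2, when the sample size is achieved, recruitment of the control group will be conducted until we reach the required sample size".

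The inference is fixed under Data Analysis: "We will use the Fisher exact test to detect any statistically significant differences in the key measures between the intervention and control groups". The threshold follows: P "values <.05 will be considered statistically significant". The Abstract names the same test. Two further comparisons are planned, one of attrition rates and one of time to return: "Third, we will compare how often both study groups return for 1 follow-up visit using a Kaplan-Meier survival analysis". Neither is described with covariates. The software list has one package for description, one for Fisher's test and one for Kaplan-Meier.

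On baseline data, Data Collection says: "In the intervention and control arms, we will collect baseline information using a questionnaire (Multimedia Appendix 1". Data Collection Tool adds: "The baseline questionnaire (Multimedia Appendix 1) will be used to collect basic demographic and household information". The items include parents' education, birth dates and employment, housing, number of children, who decides on vaccination, and household spending. Their only stated analytic use is to summarise them and "compare these characteristics between the intervention and control groups". No regression, stratification, matching or weighting appears anywhere in the article. The Limitations section mentions neither confounding nor the lack of randomisation.

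**The concern.** Under randomisation a crude 2x2 test is valid, because allocation makes the arms comparable in expectation. Here allocation is by recruitment period. If the families enrolled in one period differ systematically from those in the other, for example in education or household means, and those characteristics affect on-time return, the crude difference contains that effect. A small P value could then reflect who was enrolled rather than the reminders. A baseline table may reveal the imbalance, but the plan states no analysis that would act on it, although the data needed are already being collected.

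**Working it through.** The plan gives no figure on this point to reproduce, so the size is shown by illustration.

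**Inputs from the Protocol article.** On-time return of about 75%, 200 per arm and α = .05 (Sample Size; Data Analysis). Sidedness is not stated; two-sided is assumed.

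**Assumed inputs.** No true intervention effect. One binary covariate with odds ratio OR = 2 or 3 for on-time return. Its prevalence is 50% in the control group and 50% + d in the intervention group, where d is a systematic difference in who enrols, not chance variation.

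**Step 1: return rates by covariate level.** Solve (r0 + r1)/2 = 0.75 with r1/(1 − r1) = OR × r0/(1 − r0).
- OR 2: r0 = 68.6%, r1 = 81.4%, difference 12.77 points.
- OR 3: r0 = 65.1%, r1 = 84.9%, difference 19.72 points.

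**Step 2: bias of the crude difference.** Bias = d × (r1 − r0). For d = 20 points: 0.20 × 12.77 = 2.55 points (OR 2) and 0.20 × 19.72 = 3.94 points (OR 3).

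**Step 3: rejection rate of Fisher's test.** This uses exact enumeration over all pairs of binomial counts, with 75% in the control group and 75% + bias in the intervention group.

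| Imbalance d | Bias, OR 2 | Fisher rejects, OR 2 | Bias, OR 3 | Fisher rejects, OR 3 |
|---|---|---|---|---|
| 0 | 0 | 3.8% | 0 | 3.8% |
| 5 points | 0.64 | 4.0% | 0.99 | 4.3% |
| 10 points | 1.28 | 4.7% | 1.97 | 5.9% |
| 20 points | 2.55 | 7.4% | 3.94 | 12.8% |
| 30 points | 3.83 | 12.3% | 5.92 | 25.7% |

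**Step 4: what adjustment does.** In 4,000 simulated null trials per scenario, return rates were 85% and 65% by covariate level and the imbalance was centred on 50%. A logistic model with group and that covariate rejected in 4.7%, 5.0% and 5.0% of trials for imbalances of 10, 20 and 30 points. Fisher's test, by exact enumeration of the same scenarios, rejects in 5.9%, 12.7% and 24.6%.

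**Step 5: what adjustment does not do.** With no imbalance but an assumed 8-point calendar drift between the recruitment periods, Fisher rejected in 41% of null trials and the adjusted model in 47%.

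**Step 6: how many parameters the data can carry.** The Sample Size section gives no target rate. With 50 non-returns expected among controls (200 × 0.25), assumed intervention rates of 85%, 86.5% or 90% add 30, 27 or 20, giving 80, 77 or 70 in total. At a rule of thumb of 10 non-returns per parameter, that supports about 7 or 8 parameters. Consider mother's age, education, household type, children under 5, decision-maker and spending, with the questionnaire's substantive categories. Including group, they need 1 + 5 + 3 + 1 + 3 + 1 + 1 = 15. The list must therefore be shorter and collapsed.

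**The case against.** **The imbalance is assumed.** Both groups come from one clinic under the same eligibility criteria, in adjacent recruitment periods totalling 10 to 12 weeks. With 200 per arm and 50% prevalence, the chance standard error of a prevalence difference is √(2 × 0.25/200) = 5 points. A 20-point gap is therefore 4 standard errors and would need a systematic shift in who enrols. The documents give no evidence of one. This stands, and it is why a range is shown: up to about 10 points the effect on Fisher's error rate is small.

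**Imbalance will be visible.** Characteristics are compared between groups and tabulated, including for babies who did not return. This also stands. It would be too strong to say the covariates are not used; they are not used in the inference.

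**A covariate model could sit in an analysis plan that is not shown.** This stands only in part. The article is not silent: it names the test, the threshold and the software, and that choice does not suit the design.

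Some stronger readings are tempting but not supported:
- A reader might infer that the questionnaire holds what is needed to make the comparison unbiased. It does not. Calendar period coincides completely with group, and no baseline item can separate the two (Step 5).
- A reader using a normal approximation would find error rates of 9.2% and 15.5% at a 20-point imbalance. Those belong to the uncorrected chi-square test, not to the planned Fisher test, for which the figures are 7.4% and 12.8%.
- A reader might infer that Fisher's test is itself the fault. A true size of 3.8% is valid error control; the issue is the missing covariates, not the choice of 2x2 test.

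**Conclusion.** The point holds, limited to measured confounding. The stated inference on both key measures is unadjusted in a nonrandomised comparison, although covariates are collected in both arms. Under the assumed inputs, the false-positive rate stays below the nominal 5% at a 5-point imbalance and is close to it at 10 points. It rises to 7.4-12.8% at 20 points and 12.3-25.7% at 30. Whether the larger imbalances will occur cannot be known from the documents. A prespecified adjusted analysis is worth having because it is cheap and protects against them. The larger design threat, consecutive recruitment, remains whichever test is used.

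**What to change.** Revise Data Analysis so that, for each key measure, the main analysis is a logistic regression on group plus a short covariate list, fixed before outcomes are seen. One list that fits is mother's age (linear), mother's education in two levels, informal settlement yes/no, number of children under 5 (linear) and household spending (linear). With group, that is 6 parameters.

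- Report the standardised risk difference with a 95% CI, and keep Fisher's test as the unadjusted analysis.
- State in advance that the list will be cut, or a penalised model used, if a key measure has fewer non-returns than expected. This could happen for return to follow-up if late returners count as returned.
- State in Limitations that adjustment addresses measured confounding only and does not remove the calendar-time confounding from recruiting the arms one after the other.

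The cost is a few sentences of protocol text, slightly more analysis work in R, and the need to fix the covariates and their categories in advance. No additional data collection is required.

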### Ethical Considerations

Ethical approval was received from the Cameroon Ministry of Public Health, Northwest Regional Delegation of Health (324/ATT/NWR/RDPH/BRIGAD).

## Results

Study enrollment was planned for the beginning of 2023. Usually, the clinic schedules child vaccination 2 days per week (Tuesdays and Thursdays). Approximately 20 of 50 babies are newborns and receive their first-contact vaccine (Table 1). This means that we estimate that we will need to approach 40 of 100 parents per week to explain the study and ask for consent. We estimate we will recruit a total of 200 babies in each study group during a total period of 5 weeks (pending the response rate per week of the parents). Therefore, the total duration of recruitment might be between 10 and 12 weeks.

We expect to complete the study by July 2023 and complete the data analysis and submission of the final report by 2024. We include a dummy example of how the data will be visualized for the vaccination clinic site (Figure 1). The general characteristics of the babies in both study groups are presented in a table, including the characteristics of the babies that did not come back to the clinic. The Kaplan-Meier survival analysis will be shown as a figure.

**Figure 1 figure1:**
[figure not shown]
Fictional figure projecting how the data for patients in Bamenda who are late for their vaccination appointments will be visualized.

## Discussion

### Anticipated Findings

Child immunization is a crucial public health objective and an essential strategy in primary health care services. However, globally, there are still millions of children who are unvaccinated and at risk for VPDs. Prior to the COVID-19 pandemic, the effectiveness of automated reminders for children attending vaccination appointments was tested either by the team members of this project in the context of a refugee camp in Jordan [6,7] and the general community in Canada [3] or by other authors in Ethiopia [11], Nigeria [12], and other contexts [13,14].

The COVID-19 pandemic has also led to an increase in the number of missed follow-up doses for children. In Cameroon, the vaccination system has been weakened, and herd immunity is compromised. Also, UNICEF has warned about the impact of spreading false information (known as misinformation) about national vaccination programs in Cameroon [15]. The spreading of misinformation is considered one of the major threats to public health interventions, especially during and after COVID-19.

In this paper, we described version 1.0 of a study protocol for a nonrandomized controlled trial of child vaccination reminders in a turbulent, semiurban/semirural setting in a low-income country. The main goal of the study is to implement an automated SMS reminder system at the Bamenda primary health care center. The objectives of the study are to analyze the effect of the cellphone reminder intervention on the percentage of parent-child units returning for follow-up visits and the percentage of children receiving immunization as scheduled. Instability in northwestern Cameroon makes it important to improve childhood vaccination, and to the best of our knowledge, this is the first study to support a national vaccination program by (1) using an automated system to send reminders in the form of SMS messages and (2) send health educational messages about vaccines, as well as about parenting skills. Ames et al [16] found that childhood vaccination communications have focused on national campaigns against polio, instead of routine vaccination programs. Therefore, we think this study might have the secondary impact of promoting routine vaccination among parents.

We have previously tested this concept among refugees at the Zaatari camp in Jordan, a vulnerable group [5]. We used the same questionnaire in Jordan but provided CIMA in the form of an Android smartphone app because the majority of households in the camp owned at least one Android smartphone. The market share of smartphones in sub-Saharan Africa is growing, but they have not yet reached the majority of the population; therefore, we are using an SMS reminder system. The authors have experience in the field setting up such systems in vulnerable contexts, such as in the Central African Republic [17].

The adoption of digital health solutions is becoming important and a crucial means of enhancing the health care system in general. The testing of digital health for the improvement of childhood vaccination programs in resource-limited settings will be a great help in improving equity of access to vaccination [18]. So far, digitization has not been done in a systematic fashion, and this study in Cameroon will contribute to the learning process on how to implement and use such digital health solutions in resource-limited settings.

The outcome of this study will be of high importance for finding a holistic approach to the improvement of childhood vaccination schedules in unstable contexts such as northwest Cameroon. Parents experience stress, especially during times of uncertainty. Therefore, this study will support new studies on assessing perceptions among parents of parenting-skills health education messages sent in the form of regular SMS messages. These messages were developed by the UNODC and have been tested in different contexts around the world, including in our study of CIMA in the Zaatari camp in Jordan [5]. In our planned study in Cameroon, we will send the messages via SMS, which will be done for the first time. Finally, the results of this testing may lead to the development of a holistic approach and eventually a tool to digitally register, enhance, and monitor the vaccination schedule of children in settings such as Cameroon.

We should note that the outcome of this study will open new opportunities to explore the usefulness of automated SMS reminder systems in resource-limited settings. Childhood vaccination programs have been weakened during the COVID-19 pandemic, and we hope that our intervention will empower both parents and the vaccination clinic staff to improve vaccination coverage [19]. Finally, by improving vaccination coverage, we will be able to reduce the risk of VPD-related outbreaks in resource-limited settings.

### Limitations

We foresee the following points as potential limitations of our planned study: (1) The language context of the study is predominantly English, so the study may not be generalizable to the rest of Cameroon, where French is spoken. (2) We plan to test the effect of the SMS reminders for 1 vaccination appointment only, so further studies will be needed to ensure effectiveness over longer periods of time (for example, to ensure that parents will not have SMS fatigue). (3) The scalability of the SMS reminders needs to be evaluated from a cost-effectiveness perspective to ensure that we can provide an estimated cost for policymakers if the Ministry of Health of Cameroon scales the project (however, we performed a cost-effectiveness analysis for the CIMA-Jordan project and found that the cost was low in the context of a low-income country [20]). (4) Bamenda is considered a turbulent location due to the current crisis; this might affect the study if the situation becomes more turbulent. Such situations, labeled “armed conflicts,” are known strongly impact childhood vaccination [21], as they may lead to either forced migration of the parents out of Bamenda or short-term closure of the Azire Integrated Health Centre.

### Conclusion

There is limited evidence on effective interventions to improve childhood vaccinations in turbulent settings [14]. It is crucial to ensure parents receive reminders and correct information about all vaccines. Therefore, this project will have an impact on the health of the children and on the public health system. Also, we expect that this study will support the work of sharing correct information with parents. After the end of this study, we foresee planning to expand the implementation of CIMA to other primary health care centers in Cameroon in order to reach a larger population of children, including an evaluation of the effectiveness of the SMS reminder intervention on vaccination coverage and adherence to follow-up visits. Additionally, we will explore the potential for integrating CIMA with other health care systems, such as electronic medical records, to improve data collection and analysis.

## Appendix

Multimedia Appendix 1 Questionnaire for baseline information for the Children Immunization App (CIMA).

## Abbreviations

BCG: bacillus Calmette-Guérin
CIMA: Children Immunization App
DTP-HepB-Hib: diphtheria, tetanus, pertussis, hepatitis B, Haemophilus influenzae type b
OPV: oral polio vaccine
PCV: pneumococcal vaccine
UNICEF: United Nations Children’s Fund
UNODC: United Nations Office on Drugs and Crime
VPD: vaccine-preventable disease
WHO: World Health Organization
